## Abstract

**Background:**

Adolescents in less developed countries such as Zambia often face multi-faceted challenges for achieving successful transitions through adolescence to early adulthood. The literature has noted the need to introduce interventions during this period, particularly for adolescent girls, with the perspective that such investments have significant economic, social and health returns to society. The Adolescent Girls Empowerment Programme (AGEP) was an intervention designed as a catalyst for change for adolescent girls through themselves, to their family and community.

**Methods/design:**

AGEP was a multi-sectoral intervention targeting over 10,000 vulnerable adolescent girls ages 10–19 in rural and urban areas, in four of the ten provinces of Zambia. At the core of AGEP were mentor-led, weekly girls’ group meetings of 20 to 30 adolescent girls participating over two years. Three curricula ― sexual and reproductive health and lifeskills, financial literacy, and nutrition ― guided the meetings. An engaging and participatory pedagogical approach was used. Two additional program components, a health voucher and a bank account, were offered to some girls to provide direct mechanisms to improve access to health and financial services. Embedded within AGEP was a rigorous multi-arm randomised cluster trial with randomization to different combinations of programme arms. The study was powered to assess the impact across a set of key longer-term outcomes, including early marriage and first birth, contraceptive use, educational attainment and acquisition of HIV and HSV-2. Baseline behavioural surveys and biological specimen collection were initiated in 2013. Impact was evaluated immediately after the program ended in 2015 and will be evaluated again after two additional years of follow-up in 2017. The primary analysis is intent-to-treat. Qualitative data are being collected in 2013, 2015 and 2017 to inform the programme implementation and the quantitative findings. An economic evaluation will evaluate the incremental cost-effectiveness of each component of the intervention.

**Discussion:**

The AGEP program and embedded evaluation will provide detailed information regarding interventions for adolescent girls in developing country settings. It will provide a rich information and data source on adolescent girls and its related findings will inform policy-makers, health professionals, donors and other stakeholders.

**Trial registration:**

ISRCTN29322231. March 04 2016; retrospectively registered.

**Electronic supplementary material:**

The online version of this article (doi:10.1186/s12889-017-4280-1) contains supplementary material, which is available to authorized users.

## Background

This paper reviews the design and methods of a multi-arm, randomized cluster evaluation of the Adolescent Girls Empowerment Programme (AGEP) in Zambia. The programme was designed as a multi-sectoral intervention targeted to vulnerable, rural and urban adolescent girls ages 10–19. Embedded in the design of the programme was a rigorous, randomized evaluation that recruited a cohort of eligible adolescent girls invited to participate in the programme and girls residing in control areas. The evaluation sample was interviewed at baseline in late 2013 and early 2014 and is being tracked annually through 2017, with mid-term results collected in 2015 immediately after the end of the intervention and endline results in 2017, two years post programme termination [1].

Adolescent girls in less developed countries face a variety of risks and challenges in achieving positive and successful transitions to adulthood [2]. In Zambia, a significant proportion of girls enter marriage and/or begin childbearing early, even prior to the expected age of school leaving. As indicated by the 2013–2014 Zambia Demographic and Health Survey (DHS), nearly one in three girls aged 20–24 had married by age 18, with a similar percentage having begun childbearing [1]. The prevalence in rural areas is nearly double that of urban areas for both early marriage (39% versus 22%) and early childbearing (42% versus 21%) [3]. Not surprisingly, given rates of early marriage and childbearing, the risk of school leaving for girls during the school age years is high, with 18% of primary school age girls and 59% of secondary age girls not currently attending school [1]. The Zambia DHS also indicates that girls in Zambia begin sexual activity early, have low rates of condom use and have risk behaviours that increase their chances of acquiring sexually transmitted infections (STIs), including HIV. For instance, the median age of sexual debut is 17.7 years, approximately 1 year prior to marriage, and the prevalence of sexual initiation among 15–19 year olds is 27%. Further, of those who are currently engaging in premarital sexual activity, only 36% reported using a condom at last sex. The low rate of consistent condom use implies exposure to STIs, with 4% of adolescents 15–19 reporting having an STI or symptoms of a sexually transmitted disease and 5% having acquired HIV. The prevalence of HIV more than doubles by the time girls reach the ages of 20–24 years [1].

The literature indicates that women and adolescent girls in many less developed settings are lacking the needed assets and capacities required to make more positive and healthier transitions that would facilitate their breaking out of persistent poverty and closing the economic and livelihoods gap between men and women. In such settings, women and girls’ opportunities are inhibited by traditional practices, adverse gender norms and roles, and weak institutions and laws [4, 5]. For instance, Duflo argues that inequality, poverty and the lack of access to economic assets, opportunities and labour markets are primary drivers for the persistent disadvantage of women relative to men [5] Other studies have directly linked gender power inequality to HIV risk behaviours and exposures [6]. Women and girls who have limited social capital and are more isolated engaged in riskier sexual behaviours, are more likely exposed to sexual violence and less likely to be tested for HIV [7, 8].

To address these disadvantages, the Population Council, working in collaboration with the YWCA, Making Cents International, the National Savings and Credit Bank of Zambia (Natsave) and the Zambian Ministry of Health designed AGEP, a multi-sectoral and girl-centered intervention. The theory of change underlying AGEP (Fig. 1) proposed that working directly with adolescent girls to build their economic, health and social assets would facilitate positive change across a broad set of critical adolescent girls’ experiences and outcomes, including early marriage and first birth, schooling attainment, age of sexual debut, sexual risk behaviour, and transmission of sexually transmitted infections, including HIV. The theory underlying AGEP defines assets as a store of value that can be drawn upon by adolescent girls to address challenges and overcome vulnerabilities [9–12]. It was posited that an asset-building framework operates by enhancing girls’ knowledge and capacities, building confidence and efficacy, strengthening social networks, changing aspirations, and providing access to both health and financial services and resources. Further, it was theorized that such changes at the individual-level would percolate up to changes in the contextual environment within the family and community.

**Fig. 1 Fig1:**
[figure not shown]
AGEP Theory of Change

## Intervention design

The goal of AGEP was to reach a minimum of 10,000 adolescent girls ages 10–19 across ten sites in four of the ten provinces of Zambia; half of the sites were urban areas and half rural areas. Provinces were purposefully selected in collaboration with the donor, weighing feasibility, resources for the programme and evaluation, and the objective of representing vulnerable adolescent girls. As the programme was specifically designed to reach the most-vulnerable adolescent girls, high-density urban housing compounds were targeted, while a more general sample of rural residential communities were targeted.

### Girls group meetings

The AGEP intervention operated for a period of two years in each site from late 2013 and early 2014 through late 2015 and early 2016. Implementation of the programme was initiated sequentially by site, after the baseline evaluation survey was completed in each site. The core component of AGEP was group meetings in which 20 to 30 girls met at a local community space for one to two hours per week, most often on weekends. A community-based model was selected as school-based sexual reproductive health programs have been known to have limited impact because teachers find it hard to break out of their typical teaching styles and programs are adversely affected by an already low quality of schooling [13, 14]. In addition, school-based programs exclude out-of-school girls, which were meant to be included in the intervention. The girls’ groups were stratified by age (10–14 and 15–19) and by marital/fertility status; girls stayed with their original groups as they aged or otherwise changed status. The group sessions were based on three core curricula (Table 1) and used illustrative vignettes, role play and participatory methods to maximize impact. The meetings were led by an older, young woman from the community who had been trained to initiate and guide educational sessions and exercises on a variety of subjects. The mentors were trained in groups at central locations at the beginning of the programme, with one refresher training approximately one year into the program. Monthly mentor meetings also took place with site coordinators to address mentor questions, experiences and provide short reviews of curriculum topics.

**Table 1 Tab1:** AGEP core curricula implemented through weekly girls’ groups meetings

Health and life skills	Session topics
Introductory sessions (9 sessions)	What to expect (×2 sessions); teamwork; gender roles; communication; self-esteem; goal identification; goal setting; personal relationships
Reproductive health (9 sessions)	Life cycle; body changes; pregnancy; avoiding unintended pregnancy; reproductive myths; sexual desire; unsafe abortion, abortion and stigma; maternal mortality
Life skills (11 sessions)	Healthy relationships; reasons for delaying sex; strategies for delaying sex; passive, assertive and aggressive behaviour; drugs and alcohol; peer-pressure; decision-making; communications; managing emotions; conflict resolution
HIV, AIDs and STIs (6 sessions)	Information on transmission; myths and facts; HIV testing and counselling; risky behaviour; relationship of STIs and HIV; Stigma and discrimination
Gender and gender-based violence (4 sessions)	Sexual exploitation; avoiding and reporting sexual violence; rape and gender violence; preventing unwanted advances
Leadership (2 sessions)	Defining and identifying the qualities of leadership; community service and action
Human rights (3 sessions)	Defining human and children’s rights; sexual and reproductive health rights; HIV and AIDS and human rights.
Financial education	
Dreams (1 session)	Strengths, weakness, opportunity and threats in achieving dreams
Saving and earning money (10 sessions)	Why save, choose a savings goal, make a savings plan, banks and bank accounts, options for earning money, risky ways to earn money, difference between needs and wants, controlling spending, planning income and expenses, saving regularly
Managing money (7 sessions)	Safe places to save, dealing with setbacks in saving, own versus others money, talking about money, do’s and don’ts when talking about money, resolving conflicts over money, resolving conflicts role play
Good money management (1 session)	Journey to good money management
Nutrition	
Building blocks of nutrition (3 sessions)	Nutritional needs of adolescent girls (types of foods), role of food in the body (dietary diversity), anaemia–causes and symptoms
Nutrition in pregnancy, infancy & early childhood (3 sessions)**†**	Nutrition needs during pregnancy, infant feeding, child feeding and growth monitoring

*Note:* Two additional sessions developed for the end of the programme that helped girls to plan for “life after AGEP”. There was also an additional session for girls in Arm 3 providing details about the savings account

^**†**^denotes sessions only for girls who were aged 15 and older at baseline.

All the girls who were assigned to the intervention were invited to participate in AGEP girls’ groups. Two additional programme components were randomly assigned to some of the girls groups. The additional components were: 1) the provision of a health voucher and, 2) an offer to open a bank savings account. Eligibility for these add-on components was determined by whether or not the girl group was located in a cluster that was randomized to receive the additional components of the intervention. The assignment of girls to the programme component is discussed further in the evaluation design section below.

### Health vouchers

Girls who attended AGEP in randomly-selected areas to receive a health voucher targeted to improve access to ten general health and sexual and reproductive health services at partner public and private health providers (Table 2). The design and implementation of the AGEP health voucher was done in consultation with the Ministry of Health at the national, provincial and district level [15]. A published review of the literature found that health vouchers had been successful at increasing service utilization and improving the quality of health services provision across a variety of health care and developing country settings. The review, however, noted that the breadth and scientific quality of evidence was limited and more rigorous assessments of effectiveness were needed [16]. A study of a programme that provided health vouchers specifically to adolescent girls in Nicaragua found that it directly reduced many of the barriers to adolescent sexual reproductive health care, including improving provider knowledge around adolescent health issues, attitudes and communication practices [17]. These studies suggested the potential for improving SRH care among adolescents in Zambia and the value of implementing a voucher programme embedded within a rigorous evaluation design.

**Table 2 Tab2:** Services provided with health voucher

1	General physical exam and other non-sexual reproductive health services
2	Family planning consultation and method
3	Pregnancy testing and consultation
4	STI consultation and treatment for girl and her partner
5	HIV counselling, testing and referral
6	Antenatal care and laboratory testing
7	Comprehensive abortion care
8	Consultation for other sexual reproductive health issues
9	Cervical cancer screening
10	Gender-based violence care and referral

*Note*: Availability of services varied somewhat as not all facilities were able to provide the full list of services

In addition to the sexual and reproductive, nutritional and general health knowledge building during the weekly girls’ groups, two additional programme elements supported the AGEP health voucher component: 1) the training of health facility staff in providing adolescent girl-friendly health services, and 2) a results-based financing of service provision at health facilities [18]. All participating health facility providers and staff were given a two-day training on adolescent girl-friendly health services that followed a set curriculum specifically designed for AGEP and supported by the Ministry of Health. Monthly monitoring and quality assurance visits to health facilities were also conducted [19]. The training sessions provided an overview of AGEP and the mechanisms of the health voucher, but also covered topics geared to improve the quality of service delivery for adolescents, including values clarification about family planning, HIV and STIs, communicating and counselling adolescents, identifying and addressing barriers to adolescent health care and the sexual and reproductive health rights of adolescents.

The results-based financing component of the health voucher also provided a basis from which to reimburse the health facility and provider for service use among adolescent girls. At private and non-governmental organization facilities, AGEP reimbursements were based on negotiated fees for each service provided. At public facilities, as health services are generally free, the payments to the facilities for each service, whose rates were agreed on with MoH and were uniform for all public facilities, were distributed by fixed percentages: to the providers (50%), to the health facilities for supplies (25%), for per-diems to the district health staff to assist in monitoring service provision (20%), and to the District Health Office for overall management of the programme (5%). Reimbursements were a function of the total number of girls with vouchers obtaining services and the number of services that they accessed during the period that the vouchers were usable. It should be noted that unlike other programme elements, due to delays in finalizing the arrangements, the health voucher started after one year of the programme and continued one year after the AGEP girls groups ended.

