### Randomised cluster design

The AGEP evaluation was designed as a multi-arm randomised cluster trial where clusters within the ten study sites were randomised to receive different combinations (arms) of AGEP. The experimental and control arms of the study are displayed in Table 3, along with their associated components. Clusters assigned to the first intervention arm were assigned only the weekly girls’ group sessions. Clusters in the second intervention arm were assigned the health voucher in addition to the weekly girls’ group sessions, while clusters in the final intervention arm were assigned all components, including the bank account. The multi-arm evaluation provided for a rigorous assessment of the marginal benefit, as well as the incremental cost-effectiveness of each additional component of the intervention. All girls selected for participation in AGEP within a cluster were assigned to the intervention that was randomly selected for that cluster; girls in clusters for the control arm received neither interventions nor placebo exposures.

**Table 3 Tab3:** Randomisation arms of AGEP

Study arm	AGEP components
Intervention arm 1	Weekly girls group mentor-led sessions
Intervention arm 2	Weekly girls group mentor-led sessions + health voucher
Intervention arm 3	Weekly girls group mentor-led sessions + health voucher + bank account
Control	No components of the AGEP intervention

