### Research instruments

A household survey instrument was implemented prior to baseline to determine eligibility for the intervention and for selecting cases in designated control clusters. The household instrument included a roster of all household members with basic socio-demographic information on each member, household asset ownership, housing quality, recent household shocks, access to financial resources and distances to key resources, including schools, roads, health facilities, banks, etc. Comprehensive annual surveys were conducted at baseline and for four subsequent years. The baseline survey is included as an Additional file 1. The surveys instruments measure changes in attitudes, behaviour, transition status, social assets and cognitive skills that may occur over time regarding: educational attainment and schooling transitions; sexual activity, relationship status and sexual partners; marriage and marital dissolution; sexual and physical coercion and violence; gender attitudes, self- efficacy and locus of control; labour force participation and savings behaviour; living arrangements and household resources; mobility and migration; literacy, numeracy and cognitive skills; and ability; financial literacy and knowledge. Surveys conducted after the baseline also include questions of exposure to the intervention to address potential spillover impacts. All questionnaires were translated into Nyanja, Bemba and Kaonde.

Survey instruments were implemented by electronic data capture. Computer-Assisted Personal-Interviewing (CAPI) was used for questions that are non-sensitive. CAPI is a process of data capture in which the interviewer reads the question from a computer screen and enters the participant’s response directly into a handheld or tablet device. For sensitive questions, including sexual behaviour, sexual violence, HIV risk perception, unwanted pregnancy and abortion, Audio Computer-Assisted Self-Interviewing (ACASI) was used. With ACASI the respondent listened with headphones to pre-recorded questions and response categories, while, if desired and if the participant was literate, simultaneously reading the question on the device screen. The participant entered a response by touching a designated number or option. ACASI maximizes confidentiality and privacy of response, as no one could hear or see the question being read, nor the response option selected.

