Biological markers were collected from adolescents aged 15 and older at baseline (Round 1), after Round 3 (at the end of AGEP), and Round 5 (at the end of the evaluation). HIV status was determined via capillary blood draws obtained from finger pricks. HIV tests were conducted by trained and certified voluntary counselling and testing (VCT) staff. In accordance with Ministry of Health guidelines, we conducted serial testing using Determine™ and Uni-Gold™ [27]. Both tests have a very high sensitivity (100%) and specificity (>99%) in controlled clinic evaluations, including a controlled laboratory setting in rural Kenya [28]. The respondent was provided the test results. Post-test counseling was guided by National Guidelines for Testing and Counselling [29].

The HSV-2 biological specimens were collected via finger prick. A sample of whole blood was collected and stored in microtainers and laboratory tested. To conduct the laboratory test, serum was derived from the whole blood and the Kalon ELISA assay used, for which the sensitivity and specificity have been found to be high (92% and 98%) respectively in African populations when compared to Western Blot [30]. Indeterminate results were not retested since their prevalence was so low as to make it impractical. After specimen collection all participants were provided information about HSV-2 detection, symptoms, safe sex practices and treatment options. Respondents were provided vouchers with identification numbers to receive their test results at AGEP participating health centers. A validation of the HSV-2 laboratory testing procedures was conducted prior to testing of specimens for the main study to assure the quality of laboratory testing protocols.

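### Round 3 and Round 5 are labelled as end of programme and two years after it for every arm, but for the health voucher they fall mid-exposure and about one year after it ended

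*Protocol article*

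**What the plan says.** The section on girls group meetings gives one duration for the whole intervention: "The AGEP intervention operated for a period of two years in each site". The Background then dates the two main assessments from a single end, with "mid-term results collected in 2015 immediately after the end of the intervention and endline results in 2017, two years post programme termination". The Abstract repeats this: "Impact was evaluated immediately after the program ended in 2015 and will be evaluated again after two additional years of follow-up in 2017". Research instruments schedules the follow-up biological specimens "after Round 3 (at the end of AGEP), and Round 5 (at the end of the evaluation"). None of these statements distinguishes between arms.

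The Health vouchers section gives the voucher its own timing. Because of delays in the arrangements, and unlike the other components, "the health voucher started after one year of the programme and continued one year after the AGEP girls groups ended".

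The voucher belongs to two of the three intervention arms. "Clusters in the second intervention arm were assigned the health voucher in addition to the weekly" sessions, and Table 3 shows that arm 3 has it too. Surveys were annual: "Comprehensive annual surveys were conducted at baseline and for four subsequent years". The Analysis section makes the immediate and mediating indicators primary after Round 3, and focuses on the mediating and longer-term indicators after Round 5.

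**The concern.** Two of the three intervention arms contain a component that was still running when the programme is said to have ended. It had stopped only about a year before an endline described as two years later. The shift is disclosed once and is not carried into the statements that date the assessments.

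This matters most for the voucher's own hypotheses. The article expects the voucher to raise use of sexual and reproductive health services and of modern contraception in the immediate term, beyond what the groups achieve. In Table 4 the first is an immediate indicator and the second a mediating one, so both are primary at Round 3. Under an end-of-programme label, a null result there could be taken as the final word on a component only part delivered. A positive result could be taken as retained behaviour when it reflects access that was still open. At Round 5, a voucher increment could be reported as lasting two years when the design can show about one.

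The marginal benefit and incremental cost-effectiveness of each add-on are stated aims. Setting the voucher increment beside the groups' effect at the same round compares components at different lags.

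**Working it through.** No power formula applies; the check is a timeline in months from the start of the programme at a site.

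**Inputs**
- Groups: two years per site (Girls group meetings), so months 0 to 24.
- Voucher: starts one year in and ends one year after the groups (Health vouchers), so 0 + 12 = 12 to 24 + 12 = 36, a length of 36 − 12 = 24 months.
- Surveys: baseline plus four annual rounds (Research instruments), so Rounds 1 to 5 at about months 0, 12, 24, 36 and 48.

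**The article's own labels, checked on the groups**
- Round 3: 24 − 24 = 0 months since the groups ended.
- Round 5: 48 − 24 = 24 months since the groups ended.

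Both labels reproduce for the groups, in arms 1, 2 and 3 alike.

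**The same check on the voucher (arms 2 and 3)**
- Round 3: 24 − 12 = 12 of 24 voucher months delivered, and 36 − 24 = 12 months still to run.
- Round 4: 36 − 36 = 0 months since the voucher ended.
- Round 5: 48 − 36 = 12 months since the voucher ended, not 24.

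**Span from first to last component:** 24 months in arm 1 and 36 months in arms 2 and 3.

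**Sensitivity.** Exact survey dates are not given. Assume each round may be up to 3 months early or late:

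| | Round 3 | Round 5 |
|---|---|---|
| Months from end of groups | −3 to 3 | 21 to 27 |
| Voucher months delivered | 9 to 15 of 24 | 24 of 24 |
| Months from end of voucher | −15 to −9 | 9 to 15 |

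The mismatch for the voucher survives this range.

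**By contrast**
- Arm 1 versus control: labels correct.
- Arm 2 versus arm 1: both arms are equally far from the end of the groups; the added component is at mid-exposure (Round 3) or about one year past its end (Round 5).
- Arms 2 and 3 versus control: a package whose parts ended about 12 months apart.
- Arm 3 versus arm 2: the same voucher schedule on both sides, so no difference in voucher timing.

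**The case against.** The shift is stated openly in the Health vouchers section. The two-year duration appears under the heading for the groups, the core component shared by all intervention arms, so the end of the programme can reasonably be read as the end of the groups. On that reading the labels are correct everywhere. The Analysis section refers only to assessments after Rounds 3 and 5 and attaches no such label. The voucher's effects on service use and contraception are hypothesised for the immediate term, so measuring them while vouchers are live fits the hypothesis. Nowhere does the article say that the voucher contrast will be reported as a two-year effect.

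Much of this stands. The labels fail only for the voucher component, and the analysis text is neutral. But the Background speaks of the end of the intervention, and the voucher is part of the assigned intervention in arms 2 and 3. A reader who starts from the Abstract or Background would therefore misdate those arms.

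Two stronger inferences are tempting and should not be drawn.

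- **That the voucher contrast is biased because it mixes effect with recency.** Arms 1 and 2 were randomised, follow the same survey rounds and have the same time since the groups ended. The intention-to-treat contrast is valid for the voucher as delivered. Only its interpretation is limited.
- **That the Round 3 voucher effect is half its full size, so that (1/0.5)² = 4 times the sample would be needed.** This assumes that the effect builds linearly with exposure, which nothing in the article supports. Contraceptive use in Table 4 is a current-status measure and could be higher while vouchers are usable. The article also says that it made no detectable-effect estimates for comparisons between intervention arms, so there is no power figure for this contrast to revise.

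**Conclusion.** The point holds for the voucher component in arms 2 and 3. The dating statements in the Abstract, Background and Research instruments conflict with the Health vouchers section. At Round 3 about half of the voucher period had been delivered (12 of 24 months) and the vouchers were still usable. At Round 5 about 12 months had passed since they ended, against 24 for the groups.

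The consequence is for interpretation: what the voucher contrasts can say about an end-of-programme effect on service use and contraception, about persistence, and about the voucher's increment set beside the groups' effect. It does not touch the validity of the randomised comparisons, the sample size, or the bank-account contrast of arm 3 with arm 2. Nor should a reader infer that the voucher ran for longer than the groups: it ended a year later but lasted the same two years.

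The conclusion rests on annual rounds being close to their nominal dates and on the one-year shifts being approximate. A 3-month error in either direction leaves it unchanged.

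**What to change.** 1. Reconcile the Abstract, Background, Girls group meetings and Research instruments with the Health vouchers section by giving start, end and time since end separately for groups and voucher.
2. For arm 2 versus arm 1, and for arms 2 and 3 versus control, label Round 3 as vouchers active for about one year, and Round 5 as about two years after groups and about one year after vouchers.
3. Restrict the two-years-after statement to the groups component, where it is true in every arm.
4. Where the voucher increment is set beside the groups' effect, including in the cost-effectiveness results, state the lag for each component.
5. Report Round 4, at about month 36, as a supplementary end-of-voucher time point for service use and modern contraception. This assumes that the Round 4 questionnaire carries the same items. It cannot extend to HIV or HSV-2, since specimens are scheduled only at Rounds 1, 3 and 5.

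The cost is a few sentences and one analysis of data from a survey already in the schedule. The small downside is one more time point to report, so it should be marked as supplementary to the Round 3 and Round 5 assessments. The article describes the endline assessment as still to come, so the labels can be settled before those results are interpreted. The Round 3 relabelling applies to how the mid-term results are described from here on.
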